## Abstract

**Introduction:**

Atrial fibrillation (AF), a common arrhythmia, is associated with impaired quality of life and increased stroke risk and mortality. Clinical guidelines recommend leveraging digital technologies to support patient education and AF self-management. Conversational artificial intelligence (AI) technologies may support patient engagement with self-management by enabling human-like conversations. This study aims to evaluate the effectiveness of a conversational AI intervention (Conversational artificial intelligence HeAlth supporT in Atrial Fibrillation Self-Management (CHAT-AF-S)) in improving quality of life in patients with AF.

**Methods and analysis:**

CHAT-AF-S is a 3-month randomised controlled trial with 1:1 allocation and embedded process evaluation. We will randomise 480 adults (aged 18 years and older) with documented AF to the CHAT-AF-S intervention or usual care. Primary outcome is the Atrial Fibrillation Effect on QualiTy-of-life overall score. We will follow the intention-to-treat principles and data analysts will be blinded. Intervention participants will be invited to complete a user experience survey and take part in an interview to explore the feasibility, acceptability, perceived use and barriers and enablers to implementing the intervention. Qualitative data will be analysed thematically.

**Ethics and dissemination:**

Ethics approval was obtained from the Western Sydney Local Health District Human Ethics Research Committee (2023/ETH00765). Written and informed consent will be obtained from all study participants before commencing any study procedures. Results will be disseminated via peer-reviewed publications and presentations at international conferences.

**Trial registration number:**

Australian New Zealand Clinical Trials Registry (registration number: ACTRN12623000850673).

STRENGTHS AND LIMITATIONS OF THIS STUDYThis multicentre parallel trial with embedded process evaluation will evaluate the effect on quality of life of the Conversational HeAlth supporT in Atrial Fibrillation Self-Management intervention, a 3-month conversational artificial intelligence programme to support atrial fibrillation (AF) self-management, compared with a control group receiving standard of care.The primary outcome is the Atrial Fibrillation Effect on QualiTy-of-life overall score at 3 months, following international guideline recommendations for assessment of quality-of-life and patient-reported outcomes in AF clinical trials.Recruitment and delivery of the intervention will focus on English-speaking patients, which may limit the generalisability of the results to other populations.Due to the nature of this digital trial, participants will be aware of the assigned intervention; however, data analysis will be blinded.

## Introduction

 Atrial fibrillation (AF) is the most common arrhythmia globally and its prevalence is rapidly increasing.^1
2^ AF is associated with increased risk of stroke, heart failure and mortality.^2^ AF symptoms such as palpitations, fatigue and dyspnoea can significantly impair daily functioning and reduce quality of life.^2
3^ Guidelines emphasise patient empowerment as key to successful AF management across the components of the AF-CARE framework (C: Comorbidity and risk factor management; A: Avoid stroke and thromboembolism; R: Reduce symptoms by rate and rhythm control; E: Evaluation and dynamic reassessment).^4^ Appropriate AF management is key to improving health outcomes and quality of life for patients with AF.

Patient-centred AF management, comprising patient education, self-care support and shared decision-making, can be enhanced by technology, as indicated in recent guidelines.^4^ Digital AF patient support programmes have shown promising although mixed results,^5
6^ with some trials showing improvements in AF knowledge^7–10^ and medication adherence.^11–13^ AF quality of life was shown to improve in one trial (n=120)^14^ evaluating a non-artificial intelligence (AI) relational agent app (adjusted mean difference of 4.5 (95% CI 0.6 to 8.3) on the overall score of the Atrial Fibrillation Effect on QualiTy-of-life (AFEQT) questionnaire, at 1 month).^14^ However, the same non-AI relational agent evaluated in two larger trials (n=243, n=270) with a longer follow-up (12 months) failed to improve medication adherence or AF quality of life.^15
16^ The low levels of personalisation and ‘stickiness’ (ie, engagement propensity) of existing interventions may have limited their effectiveness and longer-term impact.

Recent advances in AI have enabled the development of voice-based conversational agents that simulate human conversation through speech recognition and natural language processing. Conversational AI can support chronic disease self-management by engaging patients in conversations about their health, but randomised controlled trials remain sparse for conversational AI in chronic disease self-management,^17
18^ particularly in AF. Our pilot trial (n=103) was the first to evaluate a voice-based conversational AI intervention for AF self-management.^19^ Although the trial was underpowered to detect between-group differences, it showed a significant quality of life improvement pre-post in the intervention group (7.1 (95% CI 2.9 to 11.3) on the AFEQT overall score) and good acceptability.^19
20^ Qualitative analysis of participant feedback on this conversational AI^20^ contributed to the development of an improved intervention, named Conversational HeAlth supporT in Atrial Fibrillation Self-Management (CHAT-AF-S). CHAT-AF-S is a 3-month self-management programme comprising automated phone calls (ie, voice-based conversational AI) and text messages to support AF self-management. The aim of this randomised controlled trial is to evaluate the effectiveness of CHAT-AF-S in improving AF quality of life.

## Methods and analysis

### Study design

This study is a multicentre, single-blind, 1:1 (intervention:control) randomised controlled trial with a 3-month follow-up, aiming to evaluate the effect of the CHAT-AF-S intervention on AF-related quality of life, compared with usual care (figure 1).^21^ The trial has been registered in the Australian and New Zealand Clinical Trials Registry (registration number: ACTRN12623000850673) and the study protocol is reported following the Standard Protocol Items: Recommendations for Interventional Trials (SPIRIT)-AI checklist^22^ for randomised controlled trial protocols (online supplemental file 1) and the mobile health evidence reporting and assessment checklist^23^ (online supplemental file 2).

**Figure 1 F1:**
[figure not shown]
Study flow diagram.

### Study setting

This study is being conducted in Western and South Western Sydney, New South Wales, Australia. Participants will be recruited from cardiology inpatient and outpatient services in Westmead Hospital and Bankstown-Lidcombe Hospital. The trial management team, located at the Westmead Applied Research Centre, is responsible for conducting and monitoring the trial across the two sites.

### Eligibility criteria

Patients are eligible to participate if they (1) are aged 18 years or older, (2) have a documented diagnosis of AF, (3) have a mobile phone that is able to receive calls, (4) are able to receive text messages and open weblinks embedded in them (self-reported), and (5) are competent with English, as ascertained by the study researcher. Participants will be excluded from the study if they (1) are on concurrent active interventional studies focused on AF education and self-management, (2) have a concomitant illness, physical impairment or mental condition which in the opinion of the study team/primary care physician could interfere with the conduct of the study including outcome assessment (eg, hearing impairment not corrected by a digital hearing aid), (3) are pregnant, (4) have a medical illness limiting life expectancy, and (5) are unable or unwilling to provide written consent.

### Recruitment

Participants will be recruited from cardiology inpatient and outpatient services at Westmead Hospital and Bankstown-Lidcombe Hospital, New South Wales, Australia. The research team and physicians will conduct weekly screening of upcoming outpatient appointments and inpatients ready for discharge to identify potentially eligible participants. The research team will approach identified patients either face-to-face during their visit or hospital admission, or over the telephone after their visit or hospital stay. The study will also be advertised through flyers in clinic waiting rooms and ward notice boards. The research team will invite eligible patients to participate in the study and provide them with a copy of the participant information and consent form (online supplemental file 3). Participants will have the opportunity to ask questions before signing the consent form.

### Intervention

#### Design and development

Participants randomised to the intervention group will receive the CHAT-AF-S programme in addition to their usual care; they will be provided with a letter to show their primary care doctor describing the AF self-management support that will be delivered by the CHAT-AF-S programme to support care coordination (online supplemental file 4). The CHAT-AF-S programme was co-designed with clinicians (cardiology and primary care), academics (expertise comprising digital health, patient engagement and behavioural science), and patients with AF, building on lessons learnt from our previous pilot trial evaluation, process evaluation and patient feedback (Australian New Zealand Clinical Trials Registry ACTRN12621000174886).^19
20
24^

The goal of CHAT-AF-S is to support patients with AF in managing their condition and thereby improve AF-related quality of life. The 3-month CHAT-AF-S programme comprises six outreaches via automated phone calls (or text-message, after three unsuccessful call attempts at 24-hour intervals) and 30 educational text messages containing AF-related information and self-management support, with links to online resources and videos (figure 2). Calls and text messages can be paused or discontinued based on participant request.

**Figure 2 F2:**
[figure not shown]
CHAT-AF-S intervention. AF, atrial fibrillation; CHAT-AF-S, Conversational HeAlth supporT in Atrial Fibrillation Self-Management; GP, general practitioner.

The educational content and structure of the CHAT-AF-S programme align with the AF-CARE framework^4^ by providing tailored education on comorbidity and risk factor management, stroke prevention, symptom management and rate and rhythm control^4^ (figure 3). The programme also enables regular assessment of risk and needs, monitoring of alerts generated by patient responses to risk assessment questions and call back from health counsellor within 2 days after an alert is triggered, with clinical escalation as needed (online supplemental file 5).^4^ Behaviour change support in CHAT-AF-S focuses on lifestyle behaviours, medication adherence and management of risk factors and symptoms, and leverages behaviour change techniques aligning with the Behaviour Change Wheel^25
26^ (online supplemental file 6).

**Figure 3 F3:**
[figure not shown]
CHAT-AF-S structure and educational content to support AF self-management. AF, atrial fibrillation; CHAT-AF-S, Conversational HeAlth supporT in Atrial Fibrillation Self-Management.

#### Automated phone calls

The automated phone calls in CHAT-AF-S are managed by a conversational AI system developed by NuanceTM (Nuance Communications Ireland Limited, Dublin, Ireland). Design and development were done in the Nuance Mix conversational AI management platform (web-based cloud service) using Mix.nlu for the natural language understanding (identifying the semantic and syntactic elements from the user utterance to interpret intent and ‘understand’ what the user says), and Mix.dialog to design the conversational interface and dialogue flows to engage the user. The application is deployed on the Nuance Dialog as a Service (DLGaaS) platform and supports automated speech recognition for Australian English. Reporting was implemented on the Nuance Insights platform connected to the Nuance DLGaaS instance. Additional platform capabilities for loading campaign lists and creating daily dialling campaigns for outbound calls are provided by EricomTM (Ericom Pty Limited, NSW, Australia) using Genesys.

The application is equipped with specific mechanisms for handling errors in recognition or understanding, including prompts paraphrasing the question and asking the user to repeat their answer, with the system moving on to the next step in the dialogue flow after two attempts. Dual-Tone Multi-Frequency backup was also available for specific questions with numbered response options (eg, call rating at the end of each call), allowing users to provide an answer by pressing keypad buttons when they encountered errors in recognition or understanding. To minimise interference from background noise in the flow of the conversation, speaking over prompts before they were complete is not supported.

#### Text messages

The CHAT-AF-S programme includes two types of text messages: call-replacement messages and scheduled educational messages. Call-replacement messages are sent to participants after three unsuccessful call attempts for one of the six outreaches. Replication of the structure and content of each of the six calls was developed in Research Electronic Data Capture (REDCap, Vanderbilt University Center for Technology Transfer and Commercialization, TN, USA), matching the call scripts, including risk and needs assessment questions with alert responses triggering an email notification to the study team. Participants access the REDCap survey through a link included in the text-message sent by the study team.

The second type of messages are scheduled educational text messages, including links to educational resources, webpages (eg, Heart Foundation), questionnaires, templates and videos. All educational resources are hosted on REDCap. Text message delivery for call-replacement messages and scheduled educational messages will be done using TextCare and DigiCuris platform (Westmead Applied Research Centre, University of Sydney, Sydney, Australia).

### Control group

The control group will receive usual care, comprising scheduled visits and clinical advice provided by their cardiologist or primary care doctor in accordance with contemporary Australian clinical guidance.^27^ This may include stroke-risk and bleeding-risk assessment, anticoagulation where indicated, rate-control or rhythm-control treatment, management of cardiovascular risk factors and comorbidities, patient education, clinical monitoring, and referral for cardioversion or catheter ablation where clinically appropriate. The specific treatments and frequency of follow-up are determined by the treating clinicians and will not be standardised by the trial.

### Outcomes

The primary outcome of this trial is the AFEQT overall score^28^ at 3 months between intervention and control groups. The AFEQT is a reliable and validated patient-reported outcome measure comprising a 21-item questionnaire with four domain scores (symptoms, daily activities, treatment concerns and treatment satisfaction) and an overall score. Scores range from 0 to 100 (higher scores associated with better quality of life). The overall AFEQT score is calculated using the symptoms, daily activity and treatment concern domain scores. A difference of 5 represents a clinically meaningful difference in AFEQT overall score.^29–31^ Choice of the primary outcome follows international guideline recommendations for assessment of quality-of-life and patient-reported outcomes in AF clinical trials^4^; this choice was further guided by our previous pilot trial ‘Coordinating Healthcare with Artificial intelligence Technology for patients with Atrial Fibrillation (CHAT-AF)’, where we found a significant pre-post improvement in AFEQT overall score in the intervention group,^19
24^ and was informed by lived experience (qualitative interviews with pilot participants and co-author investigator living with AF).^20^ The 3-month endpoint reflects the pragmatic decision to focus on short-term impact and measure the initial effect of the 3-month CHAT-AF-S intervention on the AFEQT overall score, within feasibility constraints.

Secondary outcomes include AFEQT domain subscale scores (symptoms, daily activities, treatment concerns and treatment satisfaction); pre-post AFEQT scores (overall and subscales) in the intervention group; AF knowledge measured with the Jessa Atrial Fibrillation Knowledge Questionnaire,^32^ a validated 16-item multiple choice questionnaire focusing on AF self-management and medications; Confidence in Atrial FibriLlation Management (CALM),^33^ measured with the validated 16-item CALM questionnaire; treatment burden, measured with the validated 7-domain Treatment Burden Questionnaire^34
35^; diet (measured with validated single questions for fruit intake and vegetable intake)^36^; physical activity (measured using a validated single question)^37^; alcohol intake; smoking; weight change from baseline; self-reported adherence to anticoagulant medication; and self-reported healthcare use, including primary care visits, cardiologist visits, emergency department visits, hospitalisations (online supplemental file 7).^21^ All outcomes are measured at baseline and 3 months.

### Data collection and study procedures

Eligible individuals who have provided informed consent will be asked to complete a baseline questionnaire (electronic case report form) to collect sociodemographic information. A medical history form will be completed by the research assistant by reviewing the electronic medical record. Participants in the intervention group will also complete a user experience survey to provide feedback on the intervention. REDCap software^21^ will be used for data collection. Engagement with the intervention will be assessed through intervention usage metrics. Participants in the intervention group will be invited to a semi-structured interview. We will use maximum variation sampling^38^ to interview a diverse sample of participants based on sociodemographic characteristics and their level of engagement with the intervention. The interview will be conducted via phone or online video call, audio-recorded and transcribed verbatim. We will explore: patient experiences with CHAT-AF-S, including acceptability, engagement and perceived use; barriers and enablers to engagement; and impact of the intervention on the patient journey and care integration. Interviews will be conducted until conceptual depth^39–45^ is reached (we predict a minimum of 20 patients will be interviewed and estimate that each interview will last on average 30–40 min).

### Randomisation and blinding

Randomisation will be conducted electronically via the REDCap software.^37^ The software will automatically allocate participants to the intervention or control group, according to the randomisation sequence generated in R (using the randomiseR package) and uploaded to REDCap, ensuring allocation concealment. The software will randomise participants based on allocation ratio with stratification by sex and site; allocation concealment will be ensured as the randomisation sequence will not be accessible to the study team. Due to the nature of the study, participants and hospital-based cardiologists, as well as research study staff involved in the recruitment, data collection and interviewing of participants will not be blinded. However, the statistician analysing results will be blinded to the allocation.

No information on intervention content will be provided to cardiologists in recruiting sites and only participants allocated to the intervention group will be able to access the intervention, as phone calls and text messages are delivered directly to their personal phone number. Although unlikely, contamination will be assessed using intervention access records and logs of communications with participants and clinicians; any contamination will be summarised overall, by intervention component and site. An exploratory Complier Average Treatment Effect analysis (described in Statistical considerations and data analysis section) will also reflect receipt of intervention components in each group. All analyses will be adjusted for site of recruitment and sex (stratification variables).

### Statistical considerations and data analysis

We estimated that a sample size of 480 would have 80% power to detect a difference of 7 in the overall score of the AFEQT questionnaire^28^ (α=0.05; SD=26), accounting for 10% dropout. With a difference of 5 being considered the minimal clinically important difference in AFEQT overall score,^29–31^ and based on feasibility constraints and results from previous trials,^46
47^ including our previous pilot study, a difference of 7 was used for the sample size calculation.

Statistical analysis will follow trial completion and database lock and will be conducted by a statistician blinded to group allocation, guided by a predefined statistical analysis plan. Analyses will follow the intention-to-treat principle (ie, patients will be analysed within the group to which they were randomised). We will follow a published framework for intention-to-treat analysis that accounts for missing outcome data^48^: (1) attempt to follow-up all randomised participants, even if they choose to stop receiving the allocated treatment (ie, discontinued treatment), as long as they have not withdrawn from the study; (2) perform a main analysis of all observed data that are valid under a plausible assumption about the missing data; (3) perform sensitivity analyses to explore the effect of departures from the assumption made in the main analysis; (4) account for all randomised participants in the sensitivity analyses. For the primary and secondary continuous outcomes, groups will be compared at 3 months using analysis of covariance (ANCOVA), adjusted for corresponding baseline values and stratification variables. For dichotomous outcomes, groups will be compared using a log-binomial regression, while adjusting for corresponding baseline values and stratification variables as a fixed effect. Continuous variables will be reported in means and SDs, unless they are skewed in which medians and IQR will be reported, whereas categorical variables will be reported as frequencies and/or percentages. All continuous data will be checked for normality. Appropriate methods for analysing non-normally distributed data will be used where indicated. Effect estimates will be reported with 95% CIs. All statistical tests will be two-tailed, and a significance level of 0.05 will be adopted throughout. All statistical analyses will be performed using R (V.4.1.0 or higher). We will explore heterogeneity of treatment effect by sociodemographic characteristics, CHA2DS2VA (chronic heart failure, hypertension, age ≥75 years, diabetes mellitus, prior stroke, transient ischaemic attack, or arterial thromboembolism, vascular disease, and age 65–74 years) score,^4^ recency of AF diagnosis, type of AF, and recruitment setting (inpatient vs outpatient); results will be presented displaying stratification of the outcome by subgroup. An exploratory secondary analysis will estimate the the Complier Average Treatment Effect^49
50^ to quantify the causal effect of adhering to the CHAT-AF-S intervention on the primary outcome, overall AFEQT score, provided key assumptions are met (eg, exclusion restriction; monotonicity; and Stable Unit Treatment Value Assumption). Adherence (‘treatment compliance’) will be defined a priori as meeting the minimum intervention use threshold of 4 or more outreaches completed out of 6. We will implement a two-stage least squares analysis: in the first stage, adherence (binary) will be modelled as a function of randomised assignment, and in the second stage, overall AFEQT at follow-up will be regressed on the predicted adherence from stage 1. We will also complete sensitivity analyses, defining adherence as completing 5 out of 6 outreaches and 3 out of 6 of the outreaches, as well as using a continuous adherence measure that combines outreach completion with text message engagement.

A process evaluation will be conducted following the Medical Research Council framework^51^ to assess implementation and engagement with the intervention, using intervention engagement metrics, a user experience survey, and semi-structured interviews. We will analyse engagement with the intervention using Lipschitz’s five-element standard for engagement reporting,^52^ applied to outreach completion: adherence will be defined as meeting the minimum intervention use threshold of 4 or more outreaches completed out of 6; uptake is the number of participants who complete the first outreach; frequency of use is the average number of outreaches completed per participant; and duration of use (engagement sustainment) is defined as number of participants completing the final (6th) outreach.

The MRC framework^51^ will guide exploration of how CHAT-AF-S was implemented and experienced, including engagement, acceptability (eg, satisfaction with aspects of the intervention such as content, complexity and delivery), usability, appropriateness (eg, relevance, usefulness and practicability), perceived use and contextual barriers and enablers. The Non-adoption, Abandonment, Scale-up, Spread and Sustainability framework^53^ will guide questions examining factors influencing non-adoption or abandonment and the intervention’s potential for integration into routine care, scale-up, spread and longer-term sustainability.

Data from interviews will be analysed using reflexive thematic analysis^41^ of transcribed audio recordings, using NVivo 12 (QRS International Pty Ltd, Melbourne, Victoria, Australia). The codebook will be developed by two researchers who will engage deeply with the data, discuss selected codes, and reflexively explore interpretations, documenting how different perspectives influence theme development. The codebook will be revised iteratively through discussions with additional researchers in the team and the lead investigator. Themes will be identified at a semantic level by organising data to reveal patterns in semantic content, and then by interpreting those patterns and their broader meanings and implications.^41^ Reporting will follow the Consolidated criteria for Reporting Qualitative research (COREQ) checklist for reporting qualitative research.^54^ Results will be presented anonymously, ensuring that participants cannot be re-identified in any published results.

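### Recruitment setting (inpatient or outpatient) could be added to the primary ANCOVA before database lock for a small gain in precision; the plan is valid without it

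*Protocol article*

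**What the plan says.** Under Statistical considerations and data analysis, the protocol article states for the primary and continuous secondary outcomes that "groups will be compared at 3 months using analysis of covariance (ANCOVA), adjusted for corresponding baseline values and stratification variables". Under Randomisation and blinding, "The software will randomise participants based on allocation ratio with stratification by sex and site", and the same section says that every analysis is adjusted for those two variables. The primary model therefore contains treatment, baseline AFEQT, sex and site.

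Under Recruitment, patients are identified by "weekly screening of upcoming outpatient appointments and inpatients ready for discharge", at both hospitals. Site means the hospital, and each hospital recruits in both settings, so adjusting for site does not adjust for setting.

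Setting appears in the analysis only at the end of the list of factors for exploring heterogeneity of treatment effect: "recruitment setting (inpatient vs outpatient". It must therefore be recorded for each patient.

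**The concern.** AFEQT covers symptoms and daily activities and is measured only at baseline and 3 months. A patient enrolled around a hospital stay may score below his or her usual level and recover within 3 months, while a clinic patient with the same score may be nearer a stable level. If so, a single baseline slope does not fully capture the expected 3-month score, and setting carries prognostic information beyond baseline AFEQT.

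Two things would then be lost by omitting it. Variance between settings stays in the residual. A chance difference between arms in the share of inpatients also moves the estimate and is not corrected. Recruitment is complete, so stratifying by setting is no longer possible, and covariate adjustment is the main remaining way to use it.

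**Working it through.** **Inputs from the article.** "a sample size of 480 would have 80% power to detect a difference of 7 in the overall score of the AFEQT questionnaire"; "α=0.05; SD=26), accounting for 10% dropout"; two-sided tests; 1:1 allocation; a difference of 5 taken as the minimal clinically important one.

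**Inputs not in the article (assumed).** Inpatient share f = 0.3–0.5. Gap d between settings in 3-month AFEQT at equal baseline = 5–10 points. Correlation ρ between baseline and 3-month score = 0 to 0.6, where ρ = 0 corresponds to the planning SD of 26 with no gain from baseline.

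**1. The plan's own figure.** n per arm = 2(1.960 + 0.842)² × 26² / 7² = 216.6, so 217 per arm and 434 in total. Allowing for 10% dropout gives 434/0.9 = 482.2, so 483; the variant 434 × 1.1 gives 478. The stated 480 reproduces to within a few patients. With 480 × 0.9 = 432 evaluable, 216 per arm, power is 79.9%.

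**2. Validity without setting.** In a simulation of 20,000 trials with 432 patients, the mean estimate under no effect was within 0.02 of zero. The type I error was 4.9–5.3% without setting and 5.0–5.1% with it.

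**3. Chance imbalance.** The SD of the difference between arms in inpatient share is √(2f(1−f)/216).
- f = 0.3: √(0.42/216) = 0.044
- f = 0.5: √(0.50/216) = 0.048

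The 95% range of the resulting shift is ±1.96 × SD × d.
- f = 0.3, d = 5: 1.96 × 0.0441 × 5 = 0.43 points
- f = 0.5, d = 10: 1.96 × 0.0481 × 10 = 0.94 points

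**4. Residual variance removed.** The share is f(1−f)d² / [26²(1−ρ²)]. With ρ = 0.6 the denominator is 676 × 0.64 = 432.6.
- f = 0.3, d = 5: 5.25/432.6 = 1.2%
- f = 0.5, d = 10: 25/432.6 = 5.8%

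**5. Power and interval width.** 216 per arm, f = 0.5, normal approximation. The residual SD is 26√(1−ρ²) without setting and √[676(1−ρ²) − f(1−f)d²] with it.

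| ρ | d | Power for 7: without → with | 95% CI half-width |
|---|---|---|---|
| 0 | 5 | 79.9% → 80.3% | 4.90 → 4.88 |
| 0 | 10 | 79.9% → 81.4% | 4.90 → 4.81 |
| 0.5 | 5 | 89.8% → 90.2% | 4.25 → 4.22 |
| 0.5 | 10 | 89.8% → 91.2% | 4.25 → 4.14 |
| 0.6 | 5 | 93.8% → 94.1% | 3.92 → 3.89 |
| 0.6 | 10 | 93.8% → 95.0% | 3.92 → 3.81 |

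For f = 0.5 and ρ of 0 or 0.5 the gain is about 0.4–1.5 percentage points. At f = 0.3, or with a stronger baseline correlation, it is slightly smaller.

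**The case against.** The strongest reply is that nothing in the plan is wrong. Baseline outcome plus stratification factors is a conventional, clearly specified ANCOVA. Randomisation balances setting in expectation, and the ordinary confidence interval already allows for chance imbalance in an omitted covariate. That stands, and the simulation agrees with it.

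A reader might infer three stronger claims, none of which the documents support.

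- *That the 3-month course is known to differ by setting.* No section says so, and no inpatient share is given. The Recruitment section describes screening and approach, not when AFEQT is measured, and it allows contact by telephone after the visit or stay. Eligibility needs only documented AF, so an admission need not be an acute AF episode. Baseline AFEQT would absorb at least part of any difference in level.
- *That pooling the two settings biases the primary comparison.* It does not. The shift in step 3 is part of ordinary sampling error.
- *That naming setting as a heterogeneity factor shows it belongs in the primary model.* An effect modifier is not necessarily prognostic, and the same argument would bring in every factor on that list. The listing shows only that the variable will be available.

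The reply also notes that the SAP is not shown and may add supportive adjusted analyses. That is possible, but the article states the primary model's covariates explicitly and setting is not among them. Finally, extra covariates in log-binomial regression can cause non-convergence. That stands and limits the fix.

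**Conclusion.** This is an optional efficiency improvement, not a validity flaw. The documents establish that setting is a pre-randomisation variable that will be available and that the primary model omits it. The benefit depends on an undocumented difference between settings at equal baseline. With a gap of 5–10 points and 30–50% inpatients, adjustment would guard against a chance shift of up to about 0.4–0.9 points, compared with a clinically important difference of 5. It would shorten the half-width of the interval by about 0.1 point or less. If setting is not prognostic given baseline, there is no gain and almost no loss.

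**What to change.** Before the database lock planned for mid-2026, and while the statistician is still blinded to allocation, prespecify recruitment setting (inpatient or outpatient) as an additional fixed covariate in the primary ANCOVA and in the ANCOVAs for the continuous secondary outcomes, beside baseline value, sex and site. Record the change and its date, because the same step taken after an imbalance had been seen would look data-driven.

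Do not require it in the log-binomial models, because of the risk of non-convergence.

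The cost is one degree of freedom out of more than 400 and a documented late change to a published model. No new data are needed and trial conduct does not change.
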